## Abstract

**Background:**

Persistent somatic symptoms unexplained by a defined medical or psychiatric condition often include a component of central sensitization. Many treatment options are based on cognitive behavioral therapy. Effective widely available therapies are scarce. There are self-management programs and e-therapies that aim at overcoming the central sensitization by modifying interoceptive neural networks in the brain.

**Objectives:**

This study aims to investigate the effect of a mindfulness-based amygdala and insula retraining (AIR) online program and an internet delivered therapist assisted therapy offered by Helsinki University Hospital (HUS iCBTpss) compared to treatment as usual (TAU) in the treatment of conditions causing persistent somatic symptoms.

**Methods:**

We will perform a randomized controlled trial aiming at 360 patients. Consenting patients will be randomized to three study arms: online AIR program, HUS iCBTpss (both interventions as add-ons to TAU); and TAU. Functional ability and quality of life surveys will be collected from participants at baseline and at 3, 6, and 12 months after entering the study.

**Conclusions:**

This study is one of the first to explore non-drug based online interventions developed to overcome the brain’s central sensitization and are available and accessible to patients both in primary and secondary care. The results will develop the management of the common, often debilitating persistent somatic symptoms related to many conditions unexplained by a defined somatic or psychiatric illness.

**Trial registration number:**

NCT05212467.

## Introduction

Persistent somatic symptoms (PSS) is an umbrella term to describe subjectively distressing somatic complaints, irrespective of their aetiology, that are present on most days for at least several months [1]. Often the term is used to refer to physical symptoms that cannot be attributed to any known physical or psychiatric disorder [2]. These conditions have also long been known as medically unexplained symptoms [3]. Mounting evidence shows that central nervous system and brain-body interaction has a significant role in these conditions, and recently they have been referred to as central sensitization syndromes [4].

Most likely, the origin of persistent somatic symptoms is multifactorial and includes an interaction of biological, psychological, and social factors. There is often predisposing vulnerability related to genetic or developed traits and attitudes that triggers and maintains symptoms in these conditions [5]. Usually, the onset is a consequence of stress, psychological trauma, or a stressful biological event such as a viral infection. These predisposing, triggering and maintaining factors lead to structural, functional and chemical changes in the central nervous system causing alterations in processing of internal and external stimuli, i.e. central sensitization [6]. The mechanisms of central sensitization have been widely studied among patients with chronic pain [4, 6, 7].

Chronic fatigue syndrome (ME/CFS) has been studied for at least four decades but no specific pathology or biomarker has been identified so far [8, 9]. A novel challenge causing persistent somatic symptoms is also post COVID-19 condition. It is characterized by debilitating symptoms (including breathlessness, chest pain, palpitations, and fatigue) which can last for months after the acute illness [10, 11]. The symptoms of post COVID-19 condition resemble those of other post-viral conditions, including chronic fatigue syndrome [12]. So far there is no clear explanation for the full range of symptoms in post COVID-19 condition. Researchers have suggested a broader causal model of interaction of biological, social, experiential, and psychological factors related to the condition [13]. Fibromyalgia is characterized by widespread musculoskeletal pain often associated with fatigue, sleep disturbances and other cognitive and somatic symptoms. The pathophysiology of fibromyalgia is not completely understood but abnormal central pain processing is considered as the primary pathophysiologic mechanism. Genetic factors, female sex and other painful conditions are main predisposing factors [14]. A novel study has shown association between childhood adverse events and fibromyalgia [15].

Because of the multi-factorial origin of conditions with persistent somatic symptoms, treating these disorders is considered challenging by physicians. Simultaneously these are common condition and for example in Denmark it has been estimated that 16% of the adult population suffer from them [16]. Clinics for functional disorders, psychosomatics or central sensitization syndromes are opened in many countries to develop the care of these disorders. At Helsinki University Hospital (HUS) such a clinic was opened in 2019.

Many treatment options are based on cognitive behavioral therapy (CBT). A review of randomized controlled trials assessing the efficacy of treatment for somatoform disorders indicated that CBT is the best-established treatment for a variety of these disorders [17]. Later, a Cochrane review assessed psychological therapies, especially CBT, in medically unexplained symptoms [18]. They were superior to treatment as usual or waiting list in terms of reduction of symptom severity, but effect sizes were small. Similarly, another Cochrane review found that CBT is effective in reducing the symptoms of chronic fatigue syndrome (ME/CFS) compared with usual care and may be more effective in reducing fatigue symptoms compared with other psychological therapies [19].

However, CBT is not widely available and patients suffering from persistent somatic symptoms are many. There is some evidence that CBT administered as internet therapy is effective in ME/CFS [20]. Acceptance and commitment therapy (ACT) is a form of cognitive behavioral therapy which uses acceptance and mindfulness strategies together with commitment and behavior-change strategies to strengthen behavior consistent with personal values as well as to increase psychological flexibility [21]. There is evidence that ACT in a Web-based delivery format was effective in the management of depression [22]. A web-based ACT-program has been developed by the University of Jyväskylä with expertise from the Finnish Institute of Occupational Health and is provided by the Hospital District of Helsinki and Uusimaa, which has already provided web-based treatments for various other conditions.

Easily available non-drug-based therapies are needed for the treatment of patients with persistent somatic symptoms. There is some evidence that neuroplasticity techniques may be effective in the treatment of ME/CFS [23, 24] and fibromyalgia [25] as well as post COVID-19 condition [26]. The amygdala and insula retraining program is developed by [name] and is based on the hypothesis, that in the presence of dysregulating factors (e.g. physiological stressors), the amygdala can become chronically sensitized to bodily signals by a traumatic event (e.g. viral infection) leading to a chronic over-activation of the sympathetic nervous system [24].

The insular cortex (insula) is located deep within the lateral sulcus of the brain, and a large body of evidence points to its role as the principal hub for integrating afferent information of the internal state of the body (i.e., interoception) [27–29]. The insula has an antero-posterior gradient of functional organization. The posterior insular regions receive ascending inputs from the autonomic nervous system as well as the spinal cord and brainstem nuclei, thus generating a primary interoceptive representation of the body [27, 30]. The anterior insula in turn connects to multiple other cortical regions and integrates the visceral information into emotional, cognitive and motivational conditions as well as attentional mechanisms to form a comprehensive state of awareness [30–32]. Importantly, such an interoceptive network enables conscious processing of visceral events as evidenced by functional imaging demonstrating evoked insular activity during heartrate detection tasks [33].

Furthermore, the insular interoceptive network is critically involved in sensing the state of the immune system and encoding immune responses [34, 35], but also generating the core symptoms of sickness and reorienting basic motivational states in response to peripheral inflammatory stimulus such as infection [36]. Recent evidence from experimental animals has also strikingly suggested that the insular cortex can control the peripheral immune system and ignite immune responses similar to previously experienced infections by retrieving respective immune memories (i.e., immune conditioning), which provides a hypothetical mechanism for psychogenic somatic symptoms [35].

Amygdala is a part of the subcortical limbic system with a central role in fear, threat detection and affective processing [37, 38]. It has been repeatedly linked with depressive symptoms and anxiety-related behaviors in the context of inflammation and acute sickness [39–41]. Notably, the amygdala is strongly interconnected with the insular cortex and actively involved in the processing of visceral afferent signals and the physiological state of the body [27, 36]. Meditation training has been shown to decrease the reactivity of the amygdala to emotional stimuli also during non-meditative states [42].

Given the above evidence, it is highly intriguing that behavioral interventions such as mindfulness have been demonstrated to significantly increase the mean connection strength of the insula-centered interoceptive network, suggesting that this system can be engaged and modulated by such low-cost approaches [43].

Overall, there is strong evidence of the structural and functional changes in the brain following mindfulness meditation in numerous conditions, including chronic pain, a widely studied condition of central sensitization [44–49].

The above findings set the theoretical basis for this study which will compare two online interventions: (1) mindfulness-based online amygdala and insula retraining (AIR) program, and (2) ACT based HUS internet therapy developed for persistent somatic symptoms (HUS iCBTpss), and (3) treatment as usual, in conditions causing persistent somatic symptoms (a.o. fibromyalgia, chronic fatigue syndrome (ME/CFS) and post COVID-19 condition). The study will be a randomized controlled trial performed in two clinics at Helsinki University Hospital (The Outpatient Clinic for Functional Disorders and The Outpatient Clinic for Long-term Effects of COVID-19). The trial will clarify whether internet-based non-drug therapies are helpful in overcoming the assumed central sensitization and ensuing functional disabilities caused by these conditions.

In this study we will include patients suffering from persistent somatic symptoms according to the above definition with known physical or psychiatric disorders as causes for the symptoms excluded. In addition, we will apply the specific diagnostic criteria of fibromyalgia and chronic fatigue syndrome, as well as post COVID-19 condition [10, 11, 14], all of which have elements of a dysfunctional autonomous nervous system.

We aim to explore the effect of the AIR program and the HUS iCBTpss on the patients’ self-assessment of functional ability and quality of life as compared to treatment as usual. The first hypothesis is that the AIR program is equal to the internet therapy in the management of persistent symptoms observed in bodily stress syndromes, fibromyalgia, fatigue syndrome and post COVID-19 condition. Another hypothesis is that both the AIR program and the internet therapy are more effective than treatment as usual.

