### Analysis plan

All randomized participants will be analyzed in accordance with the intention-to-treat principles. Baseline data will be summarized as counts and percentages for categorical variables and mean values with standard deviation (SD) or median values with interquartile ranges (IQRs) for normally distributed or skewed continuous variables, respectively. Changes in primary and secondary outcomes over time and differences between intervention groups will be examined using generalized linear mixed models with time (0, 3, 6 and 12 months), intervention group, and interaction between group and time as fixed effects, and participants as a random effect. The most suitable correlation structure will be determined from the data based on multiple measures, including Akaike’s and Bayesian Information Criteria. Causal Directed Acyclic Graphs will be used in order to select a minimal adjustment set of fixed effect variables for mixed modeling on repeated measures. Benjamini–Hochberg procedure will be applied to correct for multiple testing. The statistical analyses will be carried out using R statistical computing environment [58].

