### Power calculations

It is hypothesized that the AIR program is equal in effect to the e-therapy. Additionally, it is hypothesized that both the AIR program and the e-therapy are more effective than TAU. According to simulations carried out based on a previous report [25] it was estimated that a sample size of at least 90 individuals per experimental group is required for reaching statistical power of >80% for outcome measures demonstrating improvement in AIR patients as compared to treatment equivalent to relaxation therapy (RT). This sample size was sufficient for all 9 out of 9 previously studied outcome measures reflecting functional impact, clinical severity, pain catastrophizing, severity of anxiety and depressive symptoms, perceived health status, psychological inflexibility, and mindfulness at post-treatment and three-month follow up. To overcome loss to follow up, we aim at 120 patients per each treatment arm. Please see details on the power analyses in S2 Appendix.

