## Conclusion

This randomized trial assesses two online methods developed to overcome the central sensitization of the brain through a patient centered approach. The results may have an impact on the management of these common and often debilitating conditions. In addition, online programs may improve patient enablement and allow for savings in costs and more effective allocation of resources in the treatment of persistent somatic symptoms and post COVID-19 condition. If the hypothesis of the study is confirmed, further research, including cost effectiveness analyses of the novel treatment models, would bring valuable information regarding the scalability, applicability, and cost-benefits of the self-treatment programs.

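### The article hypothesises that AIR equals the internet therapy, but its stated analysis examines differences and its sample size rests on a superiority comparison, so it gives no valid route to confirming equality

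*Protocol article*

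**What the plan says.** The Introduction sets out two hypotheses. On the active comparison: "The first hypothesis is that the AIR program is equal to the internet therapy in the management of persistent symptoms". On the control comparison: "Another hypothesis is that both the AIR program and the internet therapy are more effective than treatment as usual". The Power calculations section opens with the first of these again: "It is hypothesized that the AIR program is equal in effect to the e-therapy".

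The Analysis plan section says that "differences between intervention groups will be examined using generalized linear mixed models", with group, time and their interaction as fixed effects, and that the "Benjamini–Hochberg procedure will be applied to correct for multiple testing". It names no other analysis for the equality hypothesis.

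The Power calculations section says that a "sample size of at least 90 individuals per experimental group is required for reaching statistical power of >80" per cent. That power is for improvement under AIR relative to relaxation therapy, simulated from an earlier report. The target is then raised to 120 per arm for loss to follow-up, with details in S2 Appendix.

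**The concern.** Equality is a claim that the true difference is close enough to zero. A test of difference can reject zero but cannot show closeness to it. To support equality, a trial needs a stated margin, an interval judged against that margin, and a sample large enough for the interval to fit inside it. The article's hypothesis is of this kind. Its analysis and its sizing are of the other kind, and the sizing also uses a comparator that the trial does not include.

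The mismatch works in an awkward direction. Dropout, noisy 0–10 self-ratings and multiplicity correction all make a significant difference less likely. If non-significance were taken to support equality, a weaker trial would support it more readily. At stake is what may be concluded about AIR versus the internet therapy, which the article lists as its first hypothesis.

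**Working it through.** **Inputs from the article.** 90 evaluable and 120 randomised per arm; three arms; 360 in total; primary outcomes at 6 months (functional ability 0–10, quality of life 0–10, WHODAS). The article gives no SD, margin, effect size or alpha.

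**Assumptions.** SD = 1, so differences are in SD units; two-sided 5% for a difference test; one-sided 5% for each of the two one-sided tests (TOST); normal approximation; one outcome at a time, with no multiplicity correction.

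**The plan's own figures.** 3 × 120 = 360. The implied loss is 1 − 90/120 = 25%, and 90/0.75 = 120. The 90 itself cannot be rebuilt, because the effect sizes and simulation settings are in S2 Appendix, which was not available.

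**Standard error of a difference in means.** SE = √(2/n): 0.1491 at n = 90 and 0.1291 at n = 120.

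**Chance that a real difference is non-significant.** 1 − Φ(d/SE − 1.960).

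| True difference | n = 90 | n = 120 |
|---|---|---|
| 0.20 SD | 73% | 66% |
| 0.30 SD | 48% | 36% |
| 0.40 SD | 24% | 13% |
| 0.50 SD | 8% | 3% |

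For 0.30 SD at n = 90: 0.30/0.1491 = 2.01; 2.01 − 1.96 = 0.05; Φ(0.05) ≈ 0.52; so 48% are non-significant.

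**Smallest margin with 80% TOST power, true difference 0.** (1.645 + 1.282) × SE.
- n = 90: 2.927 × 0.1491 = 0.44 SD
- n = 120: 2.927 × 0.1291 = 0.38 SD

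**With adjustment for baseline.** Multiply by √(1 − r²), where r is an assumed correlation between baseline and 6 months. This gain requires a contrast that conditions on baseline.
- r = 0.5 (factor 0.866): 0.38 SD at n = 90 and 0.33 SD at n = 120
- r = 0.7 (factor 0.714): 0.31 SD and 0.27 SD

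**TOST power by margin, unadjusted.** 2Φ(margin/SE − 1.645) − 1, set to 0 where this is negative. The last column is the n per arm for 80% power, 2 × (2.927/margin)².

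| Margin | n = 90 | n = 120 | n per arm for 80% |
|---|---|---|---|
| 0.2 SD | 0% | 0% | 429 |
| 0.3 SD | 29% | 50% | 191 |
| 0.4 SD | 70% | 85% | 108 |
| 0.5 SD | 91% | 97% | 69 |

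Margins of 0.2 to 0.3 SD are shown because the Introduction describes the advantage of psychological therapies over usual care or waiting list as small. It gives no number, so reading small as 0.2 to 0.3 SD is an assumption.

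**The case against.** Four points on the other side carry weight.

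1. A reader might infer that the investigators will report a non-significant result as equality. The article states no such rule. The Conclusion's "If the hypothesis of the study is confirmed" introduces later cost-effectiveness research, does not mention equality and sets no decision rule. The planned mixed model can also yield the 6-month contrast and its confidence interval. This stands: the finding is that non-significance would not establish equality, not that it will be misread.

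2. A margin and a confidence-interval rule are often left to an analysis plan, and the full protocol, S2 Appendix and any SAP were not available. They may contain a margin, so its absence from the article is not the finding. What remains is that the hypothesis does not fit the sizing basis and the analysis that the article itself states.

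3. A reader might infer that the sample cannot support any useful margin, or that the reachable margin would swallow the whole treatment benefit. Neither is supported. A 0.5 SD margin would have 91% to 97% power. The smallest difference detectable with 80% power at n = 90, (1.960 + 0.842) × 0.1491 = 0.42 SD, is not an expected benefit. The article gives no expected benefit over treatment as usual in SD units, and no SD or minimal important difference.

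4. The stated objective and design compare each intervention with treatment as usual, so AIR versus the internet therapy is arguably not the main conclusion. That is fair, and the superiority hypotheses are not affected. Even so, the article calls equality its first hypothesis and opens the power section with it.

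**Conclusion.** The point holds as a mismatch within the article: an equality hypothesis, an analysis of differences, and a sample size taken from a superiority comparison with a treatment outside the trial. A non-significant AIR versus internet therapy result would not confirm the hypothesis. At 0.30 SD that result would occur 48% (n = 90) or 36% (n = 120) of the time. It would be uncommon at 0.5 SD, so it should not be said that large differences would usually be missed. Benjamini–Hochberg adjustment cannot lower these percentages and may raise them.

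If equivalence is meant, the planned sample gives 80% power for margins of about 0.44 to 0.38 SD unadjusted, or 0.38 to 0.33 SD at r = 0.5. A 0.3 SD margin comes within reach only with a high baseline correlation: about 0.7 brings it within reach at 120 per arm and nearly so at 90. A 0.2 SD margin is not reached at 80% power even then. All these figures rest on the assumed SD of 1, a true difference of 0 for the equivalence calculations, and the assumed correlations.

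**What to change.** In the Introduction and in Power calculations, replace the equality hypothesis with a statement that the AIR minus internet therapy difference at 6 months will be estimated with a 95% CI, and that non-significance will not be interpreted as equality. This changes wording only. The cost is a more modest claim about AIR versus the internet therapy.

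If an equivalence claim is kept:
- Specify and justify a margin on each primary scale before any comparative data are seen by those who set it. Timing matters because the trial is ongoing, and the Study flow section gives a research assistant access to interim results.
- Judge it by TOST on the 6-month contrast, that is, by whether the 90% CI lies within the margin.
- State the power that 90 to 120 per arm gives for that margin.

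This route may cost more than wording. Without baseline adjustment, a 0.3 SD margin needs about 191 evaluable per arm and a 0.2 SD margin about 429.

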## Methods

### Design and setting of the study

The study is a multi-center randomized controlled trial exploring the effects of the mindfulness-based amygdala and insula retraining program and the HUS iCBTpss internet therapy on patient reported functional ability and quality of life in comparison to treatment as usual. We will aim at recruiting 360 volunteering patients. The SPIRIT Schedule of enrollment, interventions and assessments is shown in Fig 1. The trial design is presented in Fig 2. The protocol follows the SPIRIT guidelines (S1 Checklist. SPIRIT 2013 Checklist**).**

**Fig 1 pone.0316169.g001:**
[figure not shown]
SPIRIT schedule. Schedule of enrollment, interventions and assessments.

**Fig 2 pone.0316169.g002:**
[figure not shown]
Study design.

### Study flow

In the beginning, the patient receives written information and an oral explanation of the study from the physician and is asked to give written informed consent. Patients have the right to withdraw from the study at any point if they so wish with no consequences to their treatment.

The patients are asked to give their consent to participate in the study via the Suomi.fi-service, an electronic service requiring strong identification. The research assistant signs the consenting patients in the Helsinki University Hospital Electronic Case Report Form (HUSeCRF) system which randomizes the patients. The patients then fill in the baseline information forms online in the HUSeCRF system. The research assistant has access to the interim results. In case the research assistant reports significant differences in outcomes between intervention and control groups midway through the study, the study will be terminated earlier than planned.

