#### Treatment as usual (TAU)

The patients have an initial appointment with a physician and may in addition have appointments with a physiotherapist, an occupational therapist, a psychologist and/or a social worker. If needed, the patient can be in contact with the physician remotely (by phone or message in a patient portal) or at a control appointment. Patients may also attend group interventions. If possible, medication is kept the same during the intervention and three months afterwards. If there is need to change the medication during the trial, the changes will be recorded. We will also record the use of other simultaneous interventions (such as e.g. psychotherapy). Appointments with health professionals and attendance in group interventions are documented in the electronic patient record system.

The control group consists of treatment as usual for six months, which is the primary end point of the study. After this, control patients are offered the possibility to take part in either the AIR program or the HUS internet therapy if they so wish.

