### Outcome assessment

The primary outcomes in the study are self-reported functional ability and quality of life as measured on a scale from 0 to 10 and functional ability measured by the WHO Disability Assessment Schedule (WHODAS) instrument at six months. All outcomes of the study are presented in Table 1.

**Table 1 pone.0316169.t001:** Outcomes of the RCT and the timepoints of measurement.

	Baseline, 0 months	3 months	6 months	12 months

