**Secondary outcome measures**				
Baseline information: other chronic diseases, medications, social status, occupation	x			
Follow-up questionnaire (PREMs, treatments, feedback)		x	x	x
Quality of life: EuroHIS-QOL-8, [50]	x	x	x	x
Health related Quality of life: 15D [51]	x	x	x	x
Symptoms, SSD-12 [52] and PHQ-15 [53]	x	x	x	x
Depression, PHQ-9 [53]	x	x	x	x
Anxiety, GAD-7 [54]	x	x	x	x
ISI, Insomnia Severity Index [55]	x	x	x	x
Work ability (subjective, three steps) [56]	x	x	x	x
Resilience	x	x	x	x
Resilience Scale-14 (RS-14) [57]				
Researcher collects information from patient health record: diagnoses, medications, healthcare use, and other possible treatments during 12 months				x

In addition to the collected patient reported outcome measures (PROM), at 3, 6 and 12 months, we will collect information on patient reported experience (PREM) of the treatment received and of participating in the AIR trial.

We will perform a modifier analysis on baseline characteristics that may influence outcome impact.

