The results of the study will primarily be generalizable to other selected secondary care patients suffering from severe forms of persistent somatic symptoms. The offered treatment as usual will be received by all participating patients and it might also influence the perceived effectiveness of the interventions. An important part of the treatment relies on the patients being truly heard by the professional(s), validating their feelings, and giving them psychoeducation on their condition. The lack or inadequacy of this part of the treatment in primary health care in general (due to i.e., lacking resources or education on the conditions and their treatment) might have a significant role on the patient reported outcomes of self-management programs. Educating primary healthcare professionals working with patients suffering from persistent somatic symptoms.

on the principles and practical performance of the treatment of patients with persistent somatic symptoms might be necessary.

In this study the efficacy of the interventions will only be evaluated by subjective patient reported outcome measures. The diagnosis of persistent somatic symptoms is based upon reported subjective symptoms. Consequently, subjective symptoms are the most valid endpoints, and aiming to improve these symptoms are considered treatments [60]. Some, but not all, of the used PROMs have been validated with patients suffering from one or some of the conditions examined in this study. Quality of life and functional ability measured on a scale from 0 to 10 are susceptible to many subjective factors. On the other hand, the treatment of persistent somatic symptoms aims at improving the patient’s quality of life and functional ability most importantly from the patient’s subjective viewpoint. The systematic collection of patient-reported outcomes using several different surveys will give us indication not only of the effectiveness of the interventions but also allow for the evaluation of the sensitivity and reliability of the different PROMs in the assessment of effectiveness in treating persistent somatic symptoms. Furthermore, the investigated interventions accentuate the patients’ active role in the treatment of their persistent somatic symptoms and may enhance patient enablement.

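### Baseline questionnaires follow randomisation, so self-rated month-0 scores can be shifted by allocation if patients learn their arm first

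*Protocol article*

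**What the plan says.** The Study flow section of the Protocol article gives three steps in order. The patient consents electronically. Then: "The research assistant signs the consenting patients in the Helsinki University Hospital Electronic Case Report Form (HUSeCRF) system which randomizes the patients". The next sentence reads: "The patients then fill in the baseline information forms online in the HUSeCRF system". No other readable part of the article places the baseline forms before randomisation.

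The Abstract describes the arms: "Consenting patients will be randomized to three study arms: online AIR program, HUS iCBTpss (both interventions as add-ons to TAU); and TAU". The section on treatment as usual says that the control period lasts six months and adds: "After this, control patients are offered the possibility to take part in either the AIR program or the HUS internet therapy if they so wish". No blinding or sham is described.

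Under Outcome assessment, "The primary outcomes in the study are self-reported functional ability and quality of life as measured on a scale from 0 to 10", together with WHODAS, all at six months. Table 1 shows all three also measured at month 0. The Discussion confirms: "In this study the efficacy of the interventions will only be evaluated by subjective patient reported outcome measures".

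The baseline is used in two ways. The Analysis plan fits a mixed model in which month 0 is one of four levels of time, with terms for group and for group by time. And below Table 1: "We will perform a modifier analysis on baseline characteristics that may influence outcome impact".

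**The concern.** A baseline measure owes its value in a randomised trial to being taken before allocation can affect it. Here the written order removes that protection. Patients must know whether they have one of two online programmes or usual care alone in order to take part. They were eligible only if willing to receive an online intervention, so assignment to usual care alone may disappoint and assignment to a programme may encourage. Self-ratings from 0 to 10 are open to such reactions, and the Discussion itself calls these scales susceptible to subjective influences.

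A month-0 difference between arms that allocation has caused is not chance imbalance. An analysis that subtracts or adjusts for baseline carries it into the estimated effect. A modifier analysis on such scores would no longer be conditioning on a pre-randomisation characteristic. The direction cannot be settled from the documents. Disappointment in the control arm at month 0 would flatter that arm's later change and understate a programme's benefit; other reactions could do the reverse.

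**Working it through.** **Order of steps.** Study flow gives consent, then sign-in with randomisation, then baseline forms. It does not say when the patient is told the allocation. The exposure of the baseline to allocation is therefore possible under the text, but not established by it.

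**Which measures are exposed.** The questionnaire scores at month 0 are: the two 0 to 10 ratings, WHODAS and the self-report scales in Table 1. Age and the predefined diagnostic subgroups are eligibility facts, fixed before randomisation. Other chronic diseases, medications, social status and occupation are factual items that allocation is unlikely to alter.

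**Effect on each contrast.** Let b be the difference between two arms in month-0 mean caused by allocation, and rho the correlation between the month-0 and six-month scores. With no true effect at six months:

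- change from baseline (the group-by-time contrast of month 6 with month 0): bias of size b
- six-month score adjusted for baseline: bias of size about rho × b
- six-month score compared directly, baseline not used: bias 0

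**Benchmark.** Power calculations gives at least 90 per group for power above 80%, raised to 120 per arm. The arithmetic agrees with the target: 3 × 120 = 360, and 90 / (1 − 0.25) = 120, so the implied loss is 25%. The 90 itself comes from simulations whose inputs are in an appendix that is not shown, so it cannot be reproduced. As a yardstick, with two-sided alpha 0.05 assumed, the standardised difference detectable with 80% power at 90 per arm is (1.960 + 0.842) × √(2/90) = 0.418 SD.

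**Illustrative size.** The SD of 2 points and the shifts are assumptions; the documents give neither.

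| Shift (points) | Shift / 2 (SD) | Share of 0.418 |
|---|---|---|
| 0.2 | 0.10 | 24% |
| 0.3 | 0.15 | 36% |
| 0.5 | 0.25 | 60% |

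**Illustrative type I error.** Assumptions: no true effect, shift d in SD units, rho 0.5 to 0.7, two-sided alpha 0.05, normal approximation. The standard error is √(2(1 − rho)) × √(2/n) for the change contrast and √(1 − rho²) × √(2/n) for the adjusted contrast. The rejection probability is 1 − Φ(1.960 − bias/SE) + Φ(−1.960 − bias/SE). For example, with n = 90, rho = 0.5 and d = 0.2, the change contrast has SE = 1 × 0.149, bias/SE = 1.34, and rejection probability 27%.

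| d (SD) | Change, n = 90 | Adjusted, n = 90 | Change, n = 120 |
|---|---|---|---|
| 0.1 | 10–14% | 7–10% | 12–17% |
| 0.2 | 27–41% | 12–26% | 34–52% |
| 0.3 | 52–74% | 21–51% | 64–85% |

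A larger sample makes this worse, because the bias stays while the standard error shrinks. With forms completed before randomisation the expected month-0 difference is zero and the error rate stays at 5%.

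**The case against.** The strongest objection is that the mechanism needs a fact the article does not supply. The research assistant performs the sign-in, so an allocation can exist in the system before the patient hears of it. Figures 1 and 2 and the ethics-approved protocol, which might settle the sequence, are not shown. A reader might infer from the written order that the trial's effect estimate is biased. The documents do not support that: bias arises only if disclosure precedes the forms. What remains is that nothing stated prevents this.

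A reader might also infer that every baseline variable and modifier is compromised. As shown above, age and diagnostic subgroup are not, and the factual background items hardly so.

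Nor does the Analysis plan name month 0 as the reference or specify the primary contrast. The primary outcomes are six-month scores, and the same model can yield a direct six-month difference. The full shift b is therefore the result for one possible contrast, not for the analysis as a whole.

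Patients randomised without ever returning baseline forms are a lesser matter. Month 0 is an outcome time point in the model, so those with follow-up data stay in, and loss that differs by arm is conjecture.

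The sizes are indeed illustrative: neither the SD nor the shift has a source in the document, and 0.418 SD is a yardstick, not the trial's own design effect. Finally, since the trial is described as ongoing, reversing the order may reach few patients. That objection stands, and it makes the sensitivity analysis as important as the reversal.

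**Conclusion.** The point holds conditionally. The article states a procedure in which self-rated baselines are collected after randomisation, with recognisable arms and no described blinding. If allocation is known when the forms are completed, questionnaire-based baseline scores and modifiers can be shifted by it. Any change-from-baseline contrast then moves by the whole between-arm shift and a baseline-adjusted one by about rho times that shift. A direct six-month comparison is untouched by this particular problem.

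Under the assumed SD of 2 and shifts of 0.2 to 0.5 points, the change contrast would move by 24% to 60% of the effect detectable at 90 per arm. These figures show that modest shifts would matter; they do not estimate what has happened in this trial.

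**What to change.** Change Study flow so that all month-0 questionnaires are submitted before HUSeCRF randomises the patient, or at least before the allocation is disclosed. The cost is that a few consenting patients who never complete the forms will not be randomised, plus a change to the sequence in the electronic system, whose effort the document does not allow one to judge. The sample size does not change.

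For patients already randomised, compare the time each form was completed with the time of randomisation, and with the time of disclosure where that was recorded, and report the result by arm. Add a sensitivity analysis of the six-month between-arm difference for the three primary outcomes that does not use the self-reported baseline. This gives up the precision that baseline adjustment would bring, which is why it is a sensitivity analysis. Results for questionnaire-based modifiers should carry the same caution.

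If forms are in practice completed before patients learn their arm, correcting the Study flow text to say so is enough.
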